**Table 1 Tab1:**
[figure not shown]
Estimate of enrolment timeline

### Sample size

Sample size calculations will be based on previous studies, which report 48.3% 30-day postoperative morbidity after open surgery and 27.8% after laparoscopy [22]. The aim of the study is to show that postoperative morbidity is lower after laparoscopic surgery. Assuming *α* = 0.05 and a (?) power = 80, 87 patients are needed for both groups. The effect size is 0.54. Assuming a 10% patient drop-out rate during the 30-day follow-up period, a total of 192 patients, i.e., 96 in each group, is needed.

### Recruitment

All subjects fulfilling the inclusion criteria will be considered for participation in the trial. An anonymous record will be kept prospectively for all subjects fulfilling the inclusion criteria but not attending, either for not consenting or for any other reason, for later assessment of selection bias. The schedule of events in the study is shown in the Table 2.

**Table 2 Tab2:** SPIRIT figure

Schedule of events	Baseline	Procedure	Postoperative monitoring during hospital stay	Discharge	30 days	90 (+ 60) days	1 years	2 years	3 years	5 years	Unscheduled visit
Informed consent	X										
Need for preoperative intensive care/intensive care unit treatment	X										
Demographics and medical history	X										
Procedure details		X									
Need for postoperative intensive care/intensive care unit treatment			X								
Bowel function			X								
Analgesics			X	X							
Complications		X	X	X	X						
Gastrointestinal Quality of Life Index (GIQLI)						X					
Mortality						X					
Oncological patients: TNM classification, adjuvant chemotherapy, chemotherapy OS, CSS, DFS							X		X	X	X
Ostomy closure								X			
Protocol deviation	X	X	X	X	X		X		X	X	X

*OS* overall survival, *CSS* cancer-specific survival, *DFS* disease-free survival

## Assignment of interventions

### Allocation

Patients will be randomly allocated to the study group according to a computer-generated list, compiled by a person who is not involved in the clinical care of trial patients. The randomization will be performed in blocks of six patients. A separate randomization list will be created for each center. Another separate randomization list will be created according to the indication for surgery: obstruction, perforation, or other reason. The results of the randomization will be read by opening sealed envelopes in numerical order. Randomization will be performed after confirmation of patient eligibility and consent.

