## Methods

### Study setting

This study will be carried out in six university or central hospitals in Finland: Päijät-Häme Central Hospital, Pohjois-Karjala Central Hospital, Jorvi Helsinki University Hospital, Kanta-Häme Central Hospital, Keski-Suomi Central Hospital, and Oulu University Hospital.

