### Blinding

Blinding is impossible after surgery since wound size will reveal which technique was used. The independent surgeon evaluating the photographed surgical specimen will, however, be blinded to the technique used.

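### One published block size of six, with visible arms, lets up to a quarter of allocations be known in advance, and the text does not say how the centre and indication lists combine

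*Protocol article*

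**What the plan says.** The Allocation section describes a computer-generated list made by someone outside the clinical care of trial patients. It gives one block size: "The randomization will be performed in blocks of six patients". On list structure it says "A separate randomization list will be created for each center" and then "Another separate randomization list will be created according to the indication for surgery: obstruction, perforation, or other reason". On delivery it says "The results of the randomization will be read by opening sealed envelopes in numerical order", and on timing "Randomization will be performed after confirmation of patient eligibility and consent".

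The Blinding section adds "Blinding is impossible after surgery since wound size will reveal which technique was used". Only the surgeon who grades the specimen photographs is blinded.

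The Recruitment section provides a prospective anonymous log of eligible patients who do not take part, meant for judging selection bias later. The Trial status section reports 75 patients enrolled, against a target of 192 in the Sample size section, so the block size was published while most patients had still to be randomised.

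**The concern.** Two features of the scheme meet badly.

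First, in a fixed block of known length the later places are increasingly forced by the earlier ones. Concealed envelopes do not help if the next content can be deduced. Here the arms are visible, the sequence is kept by centre, and the block length is in print. A recruiter who works out the next arm can choose whether to approach the patient at all. The Discussion criticises the earlier retrospective literature for selection bias, and randomisation is this trial's remedy, so the concealment deserves to be as strong as is cheaply possible.

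Second, every patient has both a centre and an indication. The text names one set of lists for each factor and calls them separate, but gives no rule for which one supplies the allocation. Sites could apply it differently, and the stratification factors actually used would then be unclear at analysis.

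**Working it through.** **Inputs.** Block size 6 and three indication categories (Allocation). Six centres: "This study will be carried out in six university or central hospitals in Finland". Equal allocation, inferred from "a total of 192 patients, i.e., 96 in each group, is needed", hence three places per arm in each block. The article gives no predictability figure to reproduce.

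**Step 1: certain allocations in a complete block.** There are C(6,3) = 20 equally likely orderings. An allocation is certain when one arm has already used its three places.

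- Positions 1 to 3: never certain.
- Position 4: the first three must be identical, 2/20 = 0.10.
- Position 5: the first four must split 3:1, (4 + 4)/20 = 0.40.
- Position 6: always certain, 1.00.

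The sum is 0.10 + 0.40 + 1.00 = 1.5 per block, and 1.5/6 = 25%. If every block filled, that is 0.25 × 192 = 48 patients.

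**Step 2: unfilled last blocks.** Suppose each list stops with 0 to 5 patients in its last block, each equally likely. That block then holds 2.5 patients on average. It yields (0 + 0 + 0 + 0 + 0.1 + 0.5)/6 = 0.1 certain allocations, where the 25% rate would count 0.25 × 2.5 = 0.625. The loss is 0.525 per list.

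- Six centre lists: 48 − 6 × 0.525 = 44.85, or 23.4% of 192.
- Eighteen centre-by-indication lists: 48 − 18 × 0.525 = 38.55, or 20.1% of 192.

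Simulating 192 patients spread over the lists gives 23.4% and 20.0%. With uneven strata (assumed shares) the 18-list figure is also 20.0%.

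**Step 3: best guess.** Guessing the arm that is behind is right with probability 0.5, 0.6, 0.6, 0.7, 0.7 and 1.0 at positions 1 to 6. The sum is 4.1, and 4.1/6 = 68.3%, against 50% with no information.

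**Step 4: what varying the block size buys.** This is an exact calculation over the first 12 positions of a list. The observer is assumed to know the set of sizes, all equally likely, but not their order.

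| Block sizes | Certain allocations | Best guess right |
|---|---|---|
| 6 only | 25.0% | 68.3% |
| 4, 6 | 6.3% | 68.0% |
| 2, 4, 6 | 3.4% | 69.3% |
| 4, 6, 8 | 2.4% | 66.5% |

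Variation removes nearly all the certainty and hardly touches the best guess. Including blocks of 2 makes guessing slightly easier than it is now.

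**Step 5: the two sets of lists.** One sentence defines lists by centre and the next defines a further list by indication. Crossing them gives 6 × 3 = 18 lists with about 192/18 = 10.7 patients each. The text neither states this crossing nor excludes it.

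**Patients affected.** At the time of writing, 192 − 75 = 117 patients remained. The certain share of these would be roughly 23 (at 20%) to 29 (at 25%).

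**The case against.** A single block size is a common design choice, not an internal error, and the article contains real safeguards. The list-maker is independent, allocation follows confirmed eligibility and consent, excluded patients and reasons are documented, and eligible non-participants are logged. Surgery within 48 hours of the decision leaves limited room to delay consent. The article does not say who opens the envelopes or whether recruiters follow the sequence, and with about 11 patients per list over several years, tracking is harder than in one long list.

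Much of this stands. The 25% is a ceiling that needs staff to know the block size and to track allocations without error. The 68.3% figure is no argument for varying the block size, since variation scarcely changes it. But the safeguards do not close the gap. An independent list-maker protects how the sequence is made, not whether it can be deduced. Randomising after consent prevents a change of mind once the envelope is open, not a decision beforehand to leave a patient unapproached. The log may show such selection afterwards but does not prevent it.

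A reader might go further and infer that the two sets of lists make the scheme unworkable, for example because one indication list is shared by all six hospitals. The document says no such thing. Stratification by both factors is the natural reading, and the fault is loose wording. Nor is silence on envelope opacity a finding, since an article commonly leaves that to the full protocol.

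**Conclusion.** The concern holds as a cheap and worthwhile improvement, not as a fatal flaw. With a fixed block of six, between about 20% (18 lists) and 25% (all blocks complete) of allocations could be known in advance, with about 23% for six centre lists. These figures assume equal allocation within blocks, staff who know the block size, and accurate tracking of earlier allocations in the relevant list.

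A reader might infer that selection has occurred among the patients already enrolled. Nothing in the document supports that; the figures measure opportunity only. On the lists, the text is incomplete as written and needs one clarifying sentence.

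**What to change.** For patients not yet randomised:

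- State one scheme stratified by centre and indication (18 lists).
- Use block sizes of 4, 6 and 8 in random order, prepared by the same independent person and not disclosed to recruiting staff. Do not use blocks of 2.
- Record which list, centre or indication or both, supplied the allocation of each patient already enrolled, so that the analysis can reflect the stratification actually used.

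This brings certain allocations over the first 12 positions of a list down to about 2%. The starting point there is 25%, or nearer 20% once unfilled blocks in 18 lists are allowed for. The gain in best-guess success is small (68.3% to 66.5%) and should not be presented as the reason for the change.

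The cost is a new set of lists and envelopes and slightly looser balance in small strata. The largest possible imbalance within a block rises from three to four patients when a block of eight is in progress. If recruitment has closed by the time this is read, only the record of which list was used remains to be done.

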### Blinding

Blinding is impossible after surgery since wound size will reveal which technique was used. The independent surgeon evaluating the photographed surgical specimen will, however, be blinded to the technique used.

## Data collection, management, and analysis

### Data collection methods

All data will be collected prospectively into an electronic database.

The reasons for withdrawal will be carefully documented. The investigator will attempt to contact the subject at least three times prior to designating them as lost to follow-up. The investigator will document the date and type of attempted communication. If a subject cannot be reached during the visit window, a missed visit will be recorded. After three consecutive missed visits, the subject will be considered lost to follow-up, and a study exit form will be completed in the CRFs. Any data on subject participation and procedures until their withdrawal will be analyzed within the research.

### Data management

All data will be handled with the utmost confidentiality. Patients’ CRFs will be filled in by the study personnel during postoperative monitoring. The data will then be entered manually in the electronic database (SPSS). All patients will be supplied with a research number and the keyfile connecting research number with patient identification number stored separately from the main dataset. Both files will be placed into locked storage, accessed only by research personnel on faculty computers accessed only with a personal password. At the end of the study period, all data will be destroyed. Permission for the study register has been given by the ethics committee of Helsinki University Hospital and by the Päijät-Häme Central Hospital administration.

### Data monitoring

No data monitoring committee has been appointed for this trial. All complications and harmful events will be carefully reported using specific CRFs, and serious events will be reported to the principal investigator immediately. As previous studies do not provide enough information on differences in recovery time between open and laparoscopic approaches in an emergency setting, a preliminary safety analysis at 30-day follow-up on 50 patients in each group will be done. It is presumed that laparoscopy is safer, although there might be unknown factors that affect patient recovery. Any serious concern raised at any point in the study will result in its preliminary termination being considered. All authors will have access to the data. All concerns raised by any author or person outside the study group will be documented and assessed by the authors.

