### Statistical methods

The findings will be analyzed using SPSS (version 27 or higher) (IBM Corp., Armonk, NY, USA) for Windows. Both intention-to-treat and per-protocol analyses will be performed.

Between-group comparisons of continuous variables will be performed using Student’s *t* test or with the Mann–Whitney *U* test if heterogeneous variances persist. Categorical data will be compared using the *χ*^2^ test or Fisher’s exact test. Long-term survival will be analyzed using Cox regression or Kaplan–Meier’s analysis. Two-tailed *p* values will be reported. *P*-values ≤ 0.05 are considered significant. If data for a certain variable is missing the case will be removed from the analysis in question.

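### The interim safety look at 50 patients per group is open to all authors while recruitment continues, and the protocol does not say whether it can stop the trial only for harm

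*Protocol article*

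**What the plan says.** The Data monitoring section states that no data monitoring committee has been appointed and that "a preliminary safety analysis at 30-day follow-up on 50 patients in each group will be done". The reason given is that earlier studies say too little about differences in recovery between the two approaches in emergencies. The section adds "It is presumed that laparoscopy is safer", qualified by the possibility of unknown influences on recovery. A serious concern at any time leads to early termination being considered. No variable, direction or threshold is given. The same section says "All authors will have access to the data" and has the authors document and assess all concerns.

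Under Outcomes, the primary endpoint is 30-day morbidity measured by the Comprehensive Complication Index, built from Clavien-Dindo-graded complications. Under Blinding, only the surgeon who rates specimen photographs is blinded. Under Statistical methods, "Two-tailed *p* values will be reported" and p-values "≤ 0.05 are considered significant". The interim look is not mentioned there. Trial status reports 75 patients enrolled, so the look at 100 was still ahead.

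**The concern.** Two separate matters are at stake.

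**Conduct of the trial after the look.** The look compares the groups while nearly half of the patients are still to come, and nothing keeps the result from those who recruit, operate or grade. Someone who knows which way the difference is running may, without intending it, approach different patients, convert at a different point or grade complications differently. Grading is unblinded and feeds the primary endpoint directly. No adjustment of the significance level can repair this afterwards.

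**Meaning of the final 5% level.** The text does not say what the look may lead to. If it may stop the trial only because of harm, the final test can stand as written. If it may also end in a claim that one approach is better, testing at 0.05 on both occasions no longer gives a 5% error rate. A reader cannot tell from the document which applies.

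**Working it through.** **Inputs from the protocol article**
- Sample size: "Assuming *α* = 0.05 and a (?) power = 80, 87 patients are needed for both groups"; rates "48.3% 30-day postoperative morbidity after open surgery and 27.8% after laparoscopy"; 10% drop-out; 192 patients in total, 96 per group.
- Statistical methods: two-sided, final threshold 0.05.
- Data monitoring: look at 50 per group, 100 in total.

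**1. The plan's own figure.** With p1 = 0.483, p2 = 0.278, d = 0.205 and mean rate 0.3805, two-sided 0.05 and 80% power:

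n = [1.96·√(2·0.3805·0.6195) + 0.8416·√(0.483·0.517 + 0.278·0.722)]² / 0.205²
= (1.346 + 0.565)² / 0.04203 ≈ 86.9, so 87 per group.

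This reproduces the stated figure. Adding 10% gives 87 × 1.10 = 95.7, so 96 per group and 192 in total. The fixed-sample design is therefore a single two-sided test at 0.05, with no allowance for an earlier look.

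**2. Timing of the look.** 100/192 = 0.521 of planned enrolment, or 100/174 = 0.575 of the 2 × 87 evaluable patients. After the look, 192 − 100 = 92 patients remain, fewer if enrolment continues while the hundredth patient completes 30 days.

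**3. Error rate under each reading.** Under no difference, the interim and final statistics Z1 and Z2 are bivariate normal with correlation √t, where t is the information fraction: √0.521 = 0.722 or √0.575 = 0.758.

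| Reading of the look | Quantity | t = 0.521 | t = 0.575 |
|---|---|---|---|
| Claim possible in either direction at 0.05 | P(abs Z1 > 1.96 or abs Z2 > 1.96) | 8.24% | 8.05% |
| Stops only for laparoscopic harm; benefit tested at the end | P(Z1 > −1.96 and Z2 > 1.96) | 2.50% | 2.50% |
| Stopping for benefit needs p < 0.001; final test at 0.05 | P(abs Z1 > 3.29 or abs Z2 > 1.96) | 5.02% | 5.01% |

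The second row cannot exceed P(Z2 > 1.96) = 2.5%, because stopping for harm can only remove later claims of benefit. If harm were itself declared at nominal two-sided 0.05 at either look, the chance of any false claim would be 4.12% + 2.50% = 6.62% (t = 0.521) or 4.03% + 2.50% = 6.53% (t = 0.575). The interim threshold of 0.05 is an assumption throughout, since the document ties no p-value to the look.

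**4. Access.** No arithmetic applies here, so I compared the sections. Data monitoring gives all authors access and makes them the assessors of concerns. Data management and Confidentiality limit access to research personnel and the study group, which keeps outsiders out but not recruiting or operating authors. Data Availability concerns the final dataset. No section restricts comparative results during recruitment.

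**The case against.** The strongest reply is that this is a safety look and should be read as one. Termination is tied to serious concern, which is language about harm. No success criterion is given, and the 0.05 threshold is not linked to the interim. On that reading the false-benefit rate is unaffected. This stands, and it is why the 8% can only be conditional.

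A reader might infer more in three places.
- **That the look is a test of the primary outcome.** The section names no variable. Overlap with the Comprehensive Complication Index is likely, because both concern 30-day complications, but it remains an inference.
- **That "It is presumed that laparoscopy is safer" makes worse results after open surgery a planned reason to stop.** In context the sentence explains why laparoscopy is being checked for unexpected problems. It does not announce a benefit stop.
- **That results by group will be circulated to every author.** The text gives general access to data and does not describe how the interim result is distributed. The exposure is permitted, not stated to happen.

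Two further points are fair. Treating teams know each patient's allocation anyway, so the look adds only knowledge of the aggregate difference. And a stopping boundary is often left to a full protocol or analysis plan, neither of which is shown, so its absence alone would be no finding. But open access, assessment by the authors and the lack of a committee are stated outright. Followed as written, they leave no barrier.

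**Conclusion.** The concern holds in a limited form and should be addressed. Its firm part is access: a between-group look at 52% of planned enrolment, with about 92 patients to come, unblinded grading, and no rule keeping the result from those who recruit, operate or grade. This part does not depend on any significance level. The size of any resulting bias cannot be calculated from the document.

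The error-rate part is conditional. Overall type I error is about 8% only if the look can end in a claim at nominal two-sided 0.05. If it is harm-only, the false-benefit rate is at most 2.5% one-sided and the final 0.05 can stand. The document neither plans nor excludes a benefit stop, so it does not support saying that the 5% level is breached. It supports only saying that control of that level cannot be confirmed from the text.

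**What to change.** In Data monitoring, make two changes before the look takes place.

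1. State that the look is for harm only and makes no efficacy claim. Alternatively, state that stopping for benefit requires p < 0.001 (Haybittle-Peto), with the final test kept at 0.05.
2. Replace the sentence giving all authors access with a rule that, until recruitment closes, comparative results go only to people not involved in recruitment, surgery or complication grading. The person outside clinical care who compiled the randomisation list could prepare the tables. Recruiters are told only whether to continue or stop. The sentence on assessment of concerns by the authors should be aligned with this as far as comparative results are concerned.

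The cost is wording and restricted file access. It needs no extra patients, no new committee and no reduction of the final significance level. The small downside is that recruiting authors lose sight of comparative data until recruitment closes. Immediate reporting of individual serious events to the principal investigator is unaffected.

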### Statistical methods

The findings will be analyzed using SPSS (version 27 or higher) (IBM Corp., Armonk, NY, USA) for Windows. Both intention-to-treat and per-protocol analyses will be performed.

Between-group comparisons of continuous variables will be performed using Student’s *t* test or with the Mann–Whitney *U* test if heterogeneous variances persist. Categorical data will be compared using the *χ*^2^ test or Fisher’s exact test. Long-term survival will be analyzed using Cox regression or Kaplan–Meier’s analysis. Two-tailed *p* values will be reported. *P*-values ≤ 0.05 are considered significant. If data for a certain variable is missing the case will be removed from the analysis in question.

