### Pre-intervention data

Diagnosis and reason for the emergency operation (obstruction, perforation, ischemia etc.)Age, sex, BMI, ASA classification, co-morbidity according to the Charlson comorbidity index [28], previous abdominal operations, and medication use of anticoagulants, oral cortisone, or immunosuppressantsNeed for ICU treatment preoperatively (yes/no)

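### The lists are stratified by centre and indication, but the tests named for the primary CCI endpoint and the other continuous and categorical outcomes ignore both factors, so precision may be forgone

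*Protocol article*

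**What the plan says.** The Allocation section sets the design: "A separate randomization list will be created for each center", and then "Another separate randomization list will be created according to the indication for surgery: obstruction, perforation, or other reason". It adds "The randomization will be performed in blocks of six patients". Study setting names six hospitals. The section does not say whether the centre and indication lists are crossed.

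The Outcomes section makes 30-day morbidity, measured by the CCI on a 0–100 scale, the main endpoint. Statistical methods states "Between-group comparisons of continuous variables will be performed using" Student's t test, or the Mann–Whitney U test if variances are heterogeneous. For the rest, "Categorical data will be compared using the" chi-square or Fisher's exact test. Long-term survival is assigned to Cox regression or Kaplan–Meier, with no covariate or stratum named. Centre and indication enter no analysis anywhere in the article.

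The Pre-intervention data section lists further baseline predictors: "Age, sex, BMI, ASA classification, co-morbidity according to the Charlson comorbidity index".

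**The concern.** Stratified blocks hold the arms close to balance on centre and indication. Differences between strata then contribute little to the chance variation of the arm difference. A two-group test that ignores the strata still counts those differences as error. Its standard error is therefore larger than the true one whenever the strata predict outcome, and the test rejects less often than its nominal 5%.

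At stake is efficiency in a trial planned at 80% power, whose Discussion refers to the difficulty of recruiting in emergency settings. Indication is plausibly related to complications: the Surgical technique section describes different operative strategies for obstruction and perforation, and the investigators chose it as a stratifier. The protocol puts no number on that relation.

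**Working it through.** **1. The plan's own figure.** Inputs from the Sample size section: 48.3% and 27.8%, α = 0.05, power 80%; the test is two-sided under Statistical methods. The mean rate is (0.483 + 0.278)/2 = 0.3805 and the difference is 0.205. With pooled variance and no continuity correction:

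n = [1.960·√(2 × 0.3805 × 0.6195) + 0.842·√(0.483 × 0.517 + 0.278 × 0.722)]² / 0.205² = 86.9, i.e. 87 per group.

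The stated figure is reproduced (power 80.1%). It rests on an unadjusted two-group comparison.

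**2. Closed form for a continuous outcome, strata perfectly balanced.** In units of the outcome SD, the standard error that the unadjusted test reports is √(2/87) = 0.152. The difference detectable with 80% power is (1.960 + 0.842) × 0.152 = 0.425. The true standard error is 0.152·√(1 − R²). Hence:

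- unadjusted type I error = 2·[1 − Φ(1.960/√(1 − R²))]
- unadjusted power = Φ(0.842/√(1 − R²))
- adjusted power = Φ(2.802/√(1 − R²) − 1.960)

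| R² (assumed) | True SE | Unadjusted type I error | Power, unadjusted | Power, adjusted |
|---|---|---|---|---|
| 0 | 0.152 | 5.0% | 80.0% | 80.0% |
| 0.05 | 0.148 | 4.4% | 80.6% | 82.0% |
| 0.10 | 0.144 | 3.9% | 81.2% | 84.0% |
| 0.20 | 0.136 | 2.8% | 82.7% | 87.9% |

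**3. Simulation with incomplete blocks.** If the lists are crossed there are 6 × 3 = 18 strata, and 174/18 is about 10 patients each, so many last blocks of six stay unfilled. Two separate simulations used this layout with n = 174, comparing unadjusted tests with adjustment for the stratification factors. In simulation A (6,000 trials per setting) the outcome was normal and a t test was set against a linear model with arm, centre and indication. Stratum sizes were assumed: centres 30, 20, 15, 15, 10 and 10%; indications 50, 35 and 15%. Entries are unadjusted / adjusted, in per cent.

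| R² | A: type I error | A: power | B: type I error | B: power |
|---|---|---|---|---|
| 0 | 5.1 / 5.1 | 78.8 / 78.5 | 4.8 / 5.0 | 80 / 80 |
| 0.05 | 4.2 / 4.7 | 79.9 / 81.2 | 4.7 / 5.0 | 81 / 82 |
| 0.10 | 4.2 / 5.2 | 80.0 / 82.9 | 4.0 / 4.6 | 81 / 83 |
| 0.20 | 3.1 / 5.0 | 80.8 / 86.5 | 2.8 / 4.7 | 83 / 88 |

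In A, the standard error reported by the t test against its actual value was 0.151 against 0.146 at R² = 0.10, and 0.152 against 0.139 at 0.20. Simulation noise on a power in A is about √(0.8 × 0.2/6000) = 0.5 points. The effect size came from a normal approximation, which sets a t test slightly under 80%. The 78.8% at R² = 0, where strata play no part, reflects these two things and not a cost of ignoring the strata.

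**4. Binary outcomes.** With the planned rates, the same layout and 5,000 trials per setting, chi-square against a stratified Cochran–Mantel–Haenszel test gave power of 81.1% against 81.2% at R² of about 0.04, 82.0% against 83.9% at about 0.10, and 81.4% against 85.8% at about 0.17.

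**5. What these R² values mean.** With two equal strata around a mean morbidity of 38%, the stratum rates are 0.3805 ± √(R² × 0.3805 × 0.6195). R² = 0.05 needs about 27% and 49%, 0.10 about 23% and 53%, and 0.20 about 16% and 60%.

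**The case against.** Much of the opposing case stands.

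- **Not every comparison is a two-group test.** A reader might infer that all analyses are unadjusted. Cox regression is offered for survival and can take covariates; none is named, and none is excluded.
- **The trial is not underpowered by this choice.** That inference is tempting, but the sample size already assumed an unadjusted comparison, and in the closed form unadjusted power is at or above 80% at every R². What is forgone is a gain over the plan.
- **Validity is not threatened.** The error is on the conservative side, so no false claim of benefit follows.
- **The size rests on an assumption.** The article gives no stratum-specific outcome rates. Step 5 shows that R² of 0.10 or more needs large gaps between strata. The low end of the range, where little or nothing is gained, must be read with the rest.
- **The model is simplified.** CCI is bounded, and with the planned morbidity rates most patients would presumably score zero; the normal outcome is a convenience. Crossed lists are also assumed. If they are not crossed, a main-effects adjustment can still be used and would also correct chance imbalance.
- **Age, ASA class and the Charlson index are not stratifiers.** Collecting them does not oblige the trial to adjust, so leaving them out is no inconsistency with the design.

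The remaining objection is that covariates are usually left to an analysis plan. That would answer a complaint about silence. Here the article names the tests for each type of outcome, and those tests leave out the factors by which patients were randomised.

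**Conclusion.** The point holds as one of efficiency and of consistency between design and analysis. It covers the CCI endpoint and the other continuous and categorical outcomes. If centre and indication are prognostic, the stated tests are conservative: type I error is about 4% at R² = 0.10 and about 3% at 0.20. They then forgo about 3 and about 6 points of power. At R² = 0.05 the loss is about 1 point, and at R² = 0 there is none. Adjusting for factors that prove non-prognostic costs almost nothing (78.8% against 78.5% in simulation A). These figures assume crossed lists, 174 analysed patients and an approximately normal outcome. The direction rests only on arms balanced over prognostic strata; the size depends on R², which the protocol does not give.

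**What to change.** State the primary analysis as a linear regression of CCI on arm, centre and indication, with robust standard errors, and report the adjusted mean difference with its 95% confidence interval. Use main effects, since 18 crossed cells are too sparse for more, and set the rule for pooling very small centres in advance. For binary endpoints use Mantel–Haenszel or logistic models with the same factors. For survival use a Cox model stratified by or adjusted for indication. Keep the t, Mann–Whitney, chi-square and Fisher tests as sensitivity analyses. Say under Allocation whether the two lists are crossed. Adjustment for age and ASA class is an optional addition if prespecified.

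The cost is analysis wording only. Both factors are already recorded and the sample size need not change. The article reports 75 patients enrolled with recruitment open, so the change could be fixed before any comparison by arm, including the preliminary safety analysis at 50 patients per group.
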